## Abstract

**Background:**

In 2006 WHO presented the infant and child growth charts suggested for universal application. However, major determinants for perinatal outcomes and postnatal growth are laid down during antenatal development. Accordingly, monitoring fetal growth *in utero* by ultrasonography is important both for clinical and scientific reasons. The currently used fetal growth references are derived mainly from North American and European population and may be inappropriate for international use, given possible variances in the growth rates of fetuses from different ethnic population groups. WHO has, therefore, made it a high priority to establish charts of optimal fetal growth that can be recommended worldwide.

**Methods:**

This is a multi-national study for the development of fetal growth standards for international application by assessing fetal growth in populations of different ethnic and geographic backgrounds. The study will select pregnant women of high-middle socioeconomic status with no obvious environmental constraints on growth (adequate nutritional status, non-smoking), and normal pregnancy history with no complications likely to affect fetal growth. The study will be conducted in centres from ten developing and industrialized countries: Argentina, Brazil, Democratic Republic of Congo, Denmark, Egypt, France, Germany, India, Norway, and Thailand. At each centre, 140 pregnant women will be recruited between 8 + 0 and 12 + 6 weeks of gestation. Subsequently, visits for fetal biometry will be scheduled at 14, 18, 24, 28, 32, 36, and 40 weeks (+/− 1 week) to be performed by trained ultrasonographers.

The main outcome of the proposed study will be the development of fetal growth standards (either global or population specific) for international applications.

**Discussion:**

The data from this study will be incorporated into obstetric practice and national health policies at country level in coordination with the activities presently conducted by WHO to implement the use of the Child Growth Standards.

## Background

Of the estimated 4 million neonatal deaths each year, more than 60% are associated with low-birth-weight due to intrauterine growth restriction and/or preterm delivery [1]. Accurate prenatal assessment of fetal growth and gestational age to timely identify and adequately manage cases of growth restriction and/or preterm delivery should be considered a public health priority, especially in developing countries where 98% of the worldwide neonatal deaths occur.

Before the advent of ultrasonography, fetal growth was assessed by evaluating newborn weight as the end point of the intrauterine growth process. However, cumulative evidence indicated that this birth weight curve approach did not accurately describe the fetal growth process for newborns born before 37 weeks of pregnancy, and low birth weight babies born at term. In response to this evidence, the prenatal assessment of fetal growth and gestational age *in utero* by means of ultrasonography was adopted as standard practice in prenatal care throughout the world. The adequacy of fetal size is currently assessed by comparing the measurements of fetal anatomical parameters at a given gestational age captured through ultrasonography with reference percentiles of fetal size derived from populations of fetuses whose growth was assumed to be normal. These same reference percentiles can be used to estimate gestational age from observed fetal size. The most commonly used reference charts of size by gestational age were developed based on data from populations of fetuses in the United States or Europe. Since 1981, concerns have been raised that such charts might not be appropriate for use in other ethnic groups which may experience different patterns of fetal growth [2-4]. If fetal growth is dependent upon ethnic heritage, the potential for misclassification of fetal growth abnormalities through the wide-scale application of existing growth reference charts should generate concerns regarding diagnostic and management decisions made on the basis of ultrasonographic fetal growth assessments. Others counter argue that environmental factors play a more critical role in fetal growth than ethnicity, and that all fetuses should undergo comparable growth patterns in the absence of environmental constraints to growth [5]. The need to resolve this debate makes the development of fetal growth standards for international application both timely and a priority for improving maternal, fetal and newborn heath care worldwide [6].

Reliable standards of fetal growth are important for assessing the wellbeing of each maternal-infant dyad, determining the health status of populations, and monitoring progress in fetal and newborn health and development. Accurate fetal growth assessment is also important for maternal health. Fetal growth abnormalities are often associated with pregnancy complications such as hypertensive disorders and may affect how specific pregnancies are managed (e.g. the decision to perform a caesarean section). Thus, the results of this study will be beneficial for maternal and fetal/newborn health, they will support efforts to provide a continuum of care for mothers and their infants, and will be relevant to country efforts to accelerate progress to achieving Millennium Development Goals 1, 4, and 5.

The following sections briefly describe the work done and recommendations issued by the World Health Organization in the field of growth assessment that led to the development of this proposal.

In 2006 WHO released the WHO Child Growth Standards. These curves were the result of the WHO Multicentre Growth Reference Study (MGRS) [7] which had two characteristics that made the study unique in its field: i) the prescriptive approach [8-10]; ii) the international representation.

The proposed study is an extension of the MGRS to fetal life. It will be based on the same prescriptive approach for sample selection, and will ensure international representation by including populations from five continents. The main outcome of the study, fetal growth reference standards, will complement the MGRS by extending the WHO Child Growth Reference Charts to the prenatal period.

In 2002, a meeting of experts on the life course and health convened by the WHO Department of Non Communicable Diseases and Mental Health, Chronic Diseases and Health Promotion, identified as a top research priority, the “improvement of measures of intra-uterine growth retardation (alternative to low-birth-weight) which must reflect newborn body composition and fetal exposures that may not necessarily be expressed in birth size” [11]. Recent findings relating fetal femur length as assessed in-utero by ultrasonography with blood pressure levels in childhood confirm that measures of fetal growth alternative to birth weight provide important information which may help clarify the potential associations between fetal growth abnormalities and postnatal risk of disease [12].

In December 2002, the WHO Department of Nutrition organized a meeting of experts to review current knowledge and the practical implications of the interpretation of birth weight as a health outcome. Further research to develop fetal growth standards was identified as urgent by the group.

Finally, in 1995, the WHO Expert Committee on Physical Status published the results of a three year collaborative effort involving more than 100 experts who reviewed the currently available data on body size and composition at the different stages of life and their interpretation in terms of nutrient intake, activity level and risk of disease [13,14]. As a follow up of these recommendations, WHO implemented and conducted the MGRS. In addition, the WHO Expert Committees also recommended the development of fetal growth reference data suitable for international applications [5]. The proposed study intends to implement those recommendations as a logical extension of the MGRS.

## Methods

### Study design

This will be a multi-country observational study aiming at developing fetal growth standards for international application. This study will use an inclusive approach when selecting participating centres so that diverse ethnic population groups and diverse geographic settings are adequately represented. The following centres have been identified to participate in the study based on the proficient use of ultrasonography:

•Argentina: Centro Rosarino de Estudios Perinatales, Rosario

•Brazil: University of Campinas, Campinas

•Democratic Republic of Congo: University of Kinshasa, Kinshasa

•Denmark: Copenhagen University Rigshospitalet, Copenhagen

•Egypt: Assiut University, Assiut

•France: Hôpital Antoine Béclère, Paris

•Germany: University Medical Center, Hamburg

•India: All India Institute of Medical of Sciences, New Delhi

•Norway: University of Bergen, Bergen

•Thailand: Khon Kaen University, Khon Kaen

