### Eligibility criteria

In terms of the selection of a study participant, the protocol will follow a prescriptive approach. Participants with no known health, environmental, and/or socio-economic constraints on fetal growth will be invited to participate in the study if:

•They belong to a high socio-economic status and a high level of parental education, in order to ensure that the curves reflect, as much as possible, the true growth potential of fetuses, by limiting, as much as possible, the influence of environmental factors. Specific cut off points in family income and education have been identified by the MGRS and will be translated into socio-economic indicators specific to the countries participating in the proposed study [9,10,15];

•They live at an altitude lower than 1,500 m;

•They live near the study area. This will ensure compliance with the study, follow up for the study duration, and for potential future follow-up studies in infancy, childhood and eventually adulthood;

•They are 18 years old or more (as younger women are still growing and their babies may be smaller at birth) and ≤ 40 years;

•They have a BMI between 18–30;

•They have a singleton pregnancy;

•Their gestational age at entry is between 8 + 0 to 12 + 6 weeks based on LMP (confirmed by ultrasonography, please see Dating by ultrasound for a more detailed description);

•They have no history of health, environmental or economic constraints likely to impede fetal growth; no need for long-term medication (including fertility treatment); not smoking currently or in the previous 6 months; no history of recurrent miscarriages; and any baby previously delivered pre-term (<37 weeks) or with a birth weight <2,500 g (at 37 w 5% of boys and 10% of girls in low-risk pregnancies will be ≤2,500 g);

•There is no evidence in the present pregnancy of congenital disease or fetal anomaly. Participation in the study will cease if a major fetal anomaly is detected or serious illness develops leading to IUGR (birth weight below the 10th percentile of the recommended gender-specific birth weight for gestational age reference curves [16]); however, all mothers recruited will be followed-up until the end of the study for the purposes of describing the whole population.

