### Data analysis

Population percentiles will be calculated by applying polynomial regression methods, using the generalized estimating equations method, to model the mean at specific gestational ages, taking into account correlations between repeated measurements on the same subjects [38]. To estimate the standard deviations at each gestational age, we will use the method of the absolute residuals proposed by Altman [39]. This methodology takes into account the increase in variance with advancing gestation typical of fetal biometry data [39]. Differences in linear growth among populations of different geographical origin (categorized by study site) will be tested by evaluating the proportion of total variability in fetal biometrical measurements attributable to sites and individuals, as well as differences among sites and the effect of excluding sites on the percentiles of the total sample, as done in the MGRS [40]. The same procedure will be used to test for differences in growth related to the sex of the fetus.

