## Discussion

The data from this study, if findings are similar across diverse populations, may facilitate the adoption of an universal growth standard for international use. If heterogeneity by centre is detected despite selecting study populations according to the prescriptive approach, the study results will indicate the need to develop local/ethnically specific standards.

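### Heterogeneity between study sites supports local standards, but the stated analysis cannot support ethnically specific ones

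*Protocol article*

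**What the plan says.** - **Background** sets two positions against each other. One begins "If fetal growth is dependent upon ethnic heritage" and warns of misclassified growth; the other holds that environment matters more. It continues: "The need to resolve this debate makes the development of fetal growth standards for international application both timely and a priority".
- **Abstract, Methods** gives the main outcome as growth standards, either global or population specific.
- **Study design** seeks diversity through the choice of centres, which is to be inclusive "so that diverse ethnic population groups and diverse geographic settings are adequately represented". The ten centres, one per country, are then listed as identified "based on the proficient use of ultrasonography".
- **Eligibility criteria** contains no condition on ancestry, ethnicity or birthplace of the woman or the father. The nearest item is "They live near the study area", which is justified by compliance and follow-up. Socio-economic cut-offs are to be translated into indicators specific to each country.
- **Data analysis** states the comparison: "Differences in linear growth among populations of different geographical origin (categorized by study site) will be tested". The tools are the share of variability due to sites and to individuals, differences among sites, and the effect of leaving sites out.
- **Discussion** says that if centres turn out heterogeneous despite the prescriptive selection, "the study results will indicate the need to develop local/ethnically specific standards".

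**The concern.** Ethnicity appears in the rationale and in the conclusion, but not in the analysis that connects them. The factor tested is the centre. Two errors of reading follow. If centres differ, the Discussion allows the difference to be called ethnic although a centre differs from the next in many other ways. If centres do not differ, a reader may take the ethnic question as answered although mixed centres could hide a difference.

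The choice between one global standard and population-specific standards is the main outcome, and the Background itself ties the wrong chart to wrong diagnostic and management decisions. A chart labelled by ethnic group would be applied to women by their origin. A local chart would be applied by where they are cared for. These are different uses, and the stated analysis supports only the second.

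**Working it through.** **1. What a site contrast contains.** Let δ be a true difference in growth rate between two ethnic groups, r the share of it that survives the mix of women at two centres, and b the difference between those centres for every other reason. The observed site contrast is

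D = r·δ + b.

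The article itself shows sources of b:
- separate measurement teams at each centre (Training), although equipment and training are standardised;
- local diet, which has to be linked to country-specific food tables (Nutritional assessment);
- country-specific socio-economic cut-offs (Eligibility criteria).

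With one centre per country and no origin variable, D is one number with three unknowns behind it. Take Table 3's d for biparietal diameter, 0.1 mm per week, as an illustration:
- D = 0.1 arises from δ = 0.1, r = 1, b = 0, and equally from δ = 0, b = 0.1.
- D = 0 arises from δ = 0, b = 0, and equally from δ = 0.1, r = 0.5, b = −0.05.

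So neither a difference nor its absence identifies δ. The first pair shows that this holds even if every centre is ethnically homogeneous.

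**2. How much dilution could matter.** Table 3 (Sample size) gives 32, 23, 28, 16 and 35 women for biparietal diameter, head circumference, abdominal circumference, femur length and humerus length. Its formula is

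m = 2(z_α + z_Q)²σ²(1 − ρ) / (n·s_x²·d²).

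The table cannot be reproduced outright, because s_x² has no printed value. Solving back, two-sided, for biparietal diameter: 2(1.960 + 0.842)² × 10.2 × 0.66 / (32 × 0.1²) ≈ 330 for n·s_x². The five rows give 330 to 342, so they agree with one another. The scaling below does not need s_x².

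If one centre is wholly of the comparison group and a share f of the other centre also comes from it, then r = 1 − f. The required number becomes m/r², and power with 100 women per centre is Φ(r·√(100/m)·2.802 − 1.960). The article gives no figure for f, so the range is an assumption. The 100 is the number used for precision in Table 2.

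| f (assumed) | r | Biparietal: needed / power at 100 | Humerus: needed / power at 100 |
|---|---|---|---|
| 0 | 1.0 | 32 / 0.999 | 35 / 0.997 |
| 10% | 0.9 | 40 / 0.994 | 44 / 0.989 |
| 30% | 0.7 | 66 / 0.934 | 72 / 0.912 |
| 50% | 0.5 | 128 / 0.697 | 140 / 0.658 |

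Power stays at 80% while r is at least √(m/100): 0.59 for humerus length, 0.57 for biparietal diameter, 0.53 for abdominal circumference, 0.48 for head circumference and 0.40 for femur length. Modest mixing therefore leaves the site comparison adequately powered for Table 3's d. Step 1 carries the point; step 2 limits it.

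**The case against.** The strongest reply is that the study does not claim an ethnic test. Its aim is growth standards, the Data analysis section says openly that origin is categorised by site, and Table 3 defines d by centre. For choosing between one global chart and local charts, the resident population of a centre is a sensible unit, and a mixed centre is then the target population rather than a misclassified one. The Discussion sentence also offers *local* as one of its two alternatives. All of this stands, and it is why the site analysis need not be replaced. It does not rescue the other alternative in that sentence.

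Four stronger readings are tempting, and the document does not support them:
- **That the study sets out to settle the ethnicity question.** The debate is given as the reason why standards are needed; the stated outcome is the standards.
- **That origin is not recorded.** A condensed article does not list the enrolment items, so its silence shows nothing. What it does show is that origin plays no part in the comparison it states.
- **That mixing leaves the study underpowered.** The mix is unknown, the table shows a problem only at heavy mixing, and admixture from a third group could enlarge a contrast as well as shrink it.
- **That the spread among the four European centres (Denmark, France, Germany, Norway) could serve as a non-ethnic benchmark.** Their ethnic mix is no better known than that of the others. A standard deviation from four centres has 3 degrees of freedom, so its 95% interval runs from √(3/9.35) = 0.57 to √(3/0.216) = 3.7 times the estimate, too wide for a decision rule.

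**Conclusion.** The point holds as a mismatch between the stated analysis and one of the conclusions it is allowed to yield. Heterogeneity by centre can indicate a need for local standards. It cannot indicate a need for ethnically specific ones, and homogeneity across centres of unknown mix does not exclude an ethnic difference.

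This rests on the article's own text: no eligibility condition on origin, site as the only geographic or ethnic factor, one centre per country, and ethnicity in the conclusion. It needs no assumption about mixing. No size can be put on the bias, because neither the ethnic mix nor the non-ethnic site effects are given. A reader might infer a material loss of power; on Table 3's figures that would need the retained share to fall below 0.40 to 0.59, depending on the parameter, and nothing in the article suggests either way whether it does. The centile estimation and the sample size are not affected.

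**What to change.** 1. **Data analysis.** Keep the site comparison. Add a supportive comparison by parental origin (country of birth, or self-reported origin, of both parents), recorded at enrolment if not already collected. Repeat the site comparison restricted to women of local origin. The restriction removes the effect of mixing but not the other differences between centres. The comparison by origin is informative only as far as origin varies within centres, and the report should show how far it does.
2. **Discussion.** Let heterogeneity by centre indicate *local* standards only. Use *ethnically specific* only if the comparison by origin also differs.

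The cost is one or two enrolment items and some extra analysis; the second change needs no new data. The drawbacks are that some origin groups will be small, which is why the comparison should be supportive, and that origin is self-reported.

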### Eligibility criteria

In terms of the selection of a study participant, the protocol will follow a prescriptive approach. Participants with no known health, environmental, and/or socio-economic constraints on fetal growth will be invited to participate in the study if:

•They belong to a high socio-economic status and a high level of parental education, in order to ensure that the curves reflect, as much as possible, the true growth potential of fetuses, by limiting, as much as possible, the influence of environmental factors. Specific cut off points in family income and education have been identified by the MGRS and will be translated into socio-economic indicators specific to the countries participating in the proposed study [9,10,15];

•They live at an altitude lower than 1,500 m;

•They live near the study area. This will ensure compliance with the study, follow up for the study duration, and for potential future follow-up studies in infancy, childhood and eventually adulthood;

•They are 18 years old or more (as younger women are still growing and their babies may be smaller at birth) and ≤ 40 years;

•They have a BMI between 18–30;

•They have a singleton pregnancy;

•Their gestational age at entry is between 8 + 0 to 12 + 6 weeks based on LMP (confirmed by ultrasonography, please see Dating by ultrasound for a more detailed description);

•They have no history of health, environmental or economic constraints likely to impede fetal growth; no need for long-term medication (including fertility treatment); not smoking currently or in the previous 6 months; no history of recurrent miscarriages; and any baby previously delivered pre-term (<37 weeks) or with a birth weight <2,500 g (at 37 w 5% of boys and 10% of girls in low-risk pregnancies will be ≤2,500 g);

•There is no evidence in the present pregnancy of congenital disease or fetal anomaly. Participation in the study will cease if a major fetal anomaly is detected or serious illness develops leading to IUGR (birth weight below the 10th percentile of the recommended gender-specific birth weight for gestational age reference curves [16]); however, all mothers recruited will be followed-up until the end of the study for the purposes of describing the whole population.

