### Study procedure

Women in the first trimester (before 12 + 6 weeks gestation) attending antenatal care clinics providing ultrasonographic examinations will be approached by members of the study team and asked to participate. Women will be fully informed about the study objectives and procedures. Only women who sign a consent form will be enrolled into the study.

Fetuses will be scanned in the first trimester for the estimation of gestational age and subsequently at monthly intervals for fetal biometry [17].

All infants will receive an anthropometrical assessment after delivery, including measurement of birth weight [18]. All pregnant women in the study will be administered a 24-hour dietary recall at entry into the study, and at approximately 28 and 36 weeks gestation, to assess maternal nutritional status and ensure that women enrolled in the study have an adequate diet and that nutrient intake is in accordance with current pregnancy recommendations [18,19]. At each visit, the obstetric history of participating women will be updated to collect information related to pathological processes that may affect fetal growth, and blood pressure and proteinuria will be measured.

No additional procedures will be added to routine antenatal care provided at the study centres, with the exception of 4–5 additional ultrasonographic examinations and three repeat 24-dietary recalls.

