### Sample size

The total sample size will be 1400 pregnant women and their infants. Each country centre will collect data from 140 women. This number is sufficient for the development of local centile growth charts with a high level of precision, accounting for exclusions to final analysis due to inability to follow up and occurrence of pregnancy complications [34,35].

The sample size needed for the estimation of a specific percentile was computed using the following formula [36]:

$$n=\frac{\left(1+z_{\alpha }^{2}/2\right)}{{\left(\frac{\%\mathrm{SE}\;P_{\alpha }}{\%\mathrm{CV}}\right)}^{2}}$$

where z_α_ is the standard normal deviation corresponding to the percentile being estimated, % SE C_α_ is the expected percentage standard error of the percentile and % CV is the percentage coefficient of variation. Sample sizes were computed for 5 different parameters (biparietal diameter, abdominal and head circumference and femur and humerus length) and for 3 different percentiles: 5%, 10% and 50%. Information about the coefficient of variation was obtained from data on serial ultrasonographic examination conducted on approximately 500 pregnancies in the context of the WHO randomized trial of calcium supplementation in low intake women [37]. Additionally, the expected half-width of the confidence interval with a sample size n = 100 was computed.

Table 2 shows the levels of precision obtainable with a sample size of 100 women for various biometrical parameters. In addition the proposed sample size of 140 women per centre will allow for testing for differences in growth patterns across centres [38].

**Table 2 T2:** Levels of precision obtained with a sample size of 100 women for some biometrical fetal parameters (values and half widths in mm)

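### The withdrawal rule for serious illness depends on birth weight, so it cannot act during pregnancy; applied after delivery it selects on the growth outcome (wrong as written, minor)

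*Protocol article*

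**What the plan says.** The last bullet of Eligibility criteria gives two reasons for stopping: "Participation in the study will cease if a major fetal anomaly is detected or serious illness develops leading to IUGR". The second reason carries its definition of IUGR in a parenthesis: "serious illness develops leading to IUGR (birth weight below the 10th percentile of the recommended gender-specific birth weight for gestational age reference curves". The same bullet adds that "all mothers recruited will be followed-up until the end of the study for the purposes of describing the whole population". It does not say whether the scans of women who stop enter the centiles.

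Study procedure places the deciding measurement after birth: "All infants will receive an anthropometrical assessment after delivery, including measurement of birth weight". It also says that at each visit "the obstetric history of participating women will be updated to collect information related to pathological processes that may affect fetal growth", with blood pressure and proteinuria measured as well. The article gives no criterion for IUGR that could be applied before delivery.

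Sample size justifies 140 women per centre as "accounting for exclusions to final analysis due to inability to follow up and occurrence of pregnancy complications". That wording has no birth-weight condition. Data analysis does not say who contributes to the centiles.

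**The concern.** A rule for ending participation needs information that exists while the woman is still participating. A major anomaly can be seen at the 18-24 week scan. A birth weight below a percentile cannot be seen before delivery, and delivery ends the scans.

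If the rule is applied afterwards, it no longer removes a constraint on growth, which is the aim of the prescriptive approach. It removes a result. Ill women with larger babies stay and ill women with smaller babies go, and birth weight is closely tied to the late scans. The cut-off comes from an existing birth-weight curve, while the Abstract motivates the study by saying that current fetal growth references "may be inappropriate for international use". That doubt concerns ultrasound references, so the parallel is one of principle. Still, one fixed external cut-off removes unequal shares of ill women at centres whose babies differ in size.

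At stake are the 5th and 10th centiles, which define smallness, and the centre comparison, which the Discussion uses to choose between a universal standard and local ones.

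**Working it through.** **1. The plan's own precision.** For abdominal circumference at week 36, Table 2 gives mean 314.5 mm, 10th centile 288.0 mm and CV 7.1%. The Sample size formula with n = 100 gives %SE = 7.1 × √((1 + 1.2816²/2)/100) = 0.958, printed as 0.96. Half-width = 2 × 0.00958 × 288.0 = 5.52 mm, as printed. The SD is 0.071 × 314.5 = 22.3 mm. Ten centres of 100 women pooled give about 5.52/√10 = 1.75 mm.

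**2. Share of ill women removed.** If illness lowers birth weight by e SD and a centre lies c SD below the reference, the share is Φ(−1.2816 + e + c).
- e = 0.5: Φ(−0.782) = 22% at a matching centre; Φ(−0.282) = 39% at a centre 0.5 SD smaller.
- e = 1.0: Φ(−0.282) = 39%; Φ(0.218) = 59%.

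In women per centre, with 5% ill and e = 0.5, this is 140 × 0.05 × 0.217 = 1.5 against 140 × 0.05 × 0.389 = 2.7. With 10% ill and e = 1.0 it is 140 × 0.10 × 0.389 = 5.4 against 140 × 0.10 × 0.586 = 8.2.

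**3. Effect on the 10th centile.** Illness frequency, illness effect and the correlation of late scan with birth weight (0.7) are assumptions; the article gives none of them. The model is bivariate normal, simulated with 4 million pregnancies. The 10th centile is mean − 1.2816 × SD, with the SD from absolute residuals. Illness is first taken to lower scan and birth weight equally. Shifts in SD are against removing nobody; the last column is (A − B) × 22.3 mm.

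| Centre | Ill, effect | A: ill and small removed | B: all ill removed | A − B (mm) |
|---|---|---|---|---|
| Matching | 5%, 0.5 SD | 0.027 | 0.032 | −0.1 |
| Matching | 10%, 0.5 SD | 0.053 | 0.064 | −0.2 |
| Matching | 10%, 1.0 SD | 0.117 | 0.154 | −0.8 |
| Matching | 15%, 0.75 SD | 0.119 | 0.157 | −0.9 |
| Matching | 15%, 1.0 SD | 0.171 | 0.228 | −1.3 |
| 0.5 SD smaller | 5%, 0.5 SD | 0.036 | 0.032 | +0.1 |
| 0.5 SD smaller | 10%, 0.5 SD | 0.072 | 0.064 | +0.2 |
| 0.5 SD smaller | 10%, 1.0 SD | 0.146 | 0.154 | −0.2 |
| 0.5 SD smaller | 15%, 0.75 SD | 0.155 | 0.157 | 0.0 |
| 0.5 SD smaller | 15%, 1.0 SD | 0.215 | 0.228 | −0.3 |

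If illness lowers the scan only 0.7 times as much as birth weight, A − B runs from about −0.3 to +0.4 mm in these scenarios. One further corner (15% ill, 0.5 SD, smaller centre) gives +0.6 mm.

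**4. If ill women are not removed at all.** Against B, the 10th centile is lower by up to 0.157 × 22.3 = 3.5 mm, or 0.228 × 22.3 = 5.1 mm in the 15%, 1.0 SD corner.

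**5. Between centres.** Rule A shifts the smaller centre more than the matching one by at most (0.215 − 0.171) × 22.3 = 1.0 mm. Rule B shifts both equally.

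**The case against.** The strongest reply is that this is loose wording with little effect. Excluding pathology is the purpose of a prescriptive standard, so a rise in the 10th centile when ill pregnancies leave is intended. The right comparison is the stated rule against a clean diagnosis-based rule, and that difference is small. This stands, and it sets the size given here.

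Three stronger readings are tempting, and the article does not support them.
- A reader might infer that every baby below the 10th percentile is removed, which would raise the 5th centile by roughly 4 to 11 mm. The rule also requires serious illness, so this does not follow.
- A reader might infer that each centre will apply the rule in its own way. The article does not say who applies it, and Data management describes one online system checked by the WHO coordinating unit.
- A reader might infer that ill women stay in the centiles. The Sample size wording, with follow-up kept for description, points the other way, although no sentence settles it.

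The Sample size sentence explains an attrition allowance and need not be a separate rule. The detailed list of illnesses may also stand in the full protocol. Neither point repairs a stated trigger that depends on a measurement taken after delivery.

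**Conclusion.** Wrong as written, minor. The timing fault and the selection on outcome follow from the text alone, and the two sections describe the exclusion differently. The numerical effect rests on assumed illness frequency, illness effect and correlation. Over 5-15% ill and 0.5-1.0 SD, the literal and diagnosis-based rules differ by about −1.3 to +0.4 mm in the 10th centile of abdominal circumference at week 36 (+0.6 mm in the one extra corner). That is below both the per-centre and the pooled half-width. The distortion of the centre comparison is also small, at most about 1 mm against 5.52 mm per centre. An illness frequency of 15% is probably high for women selected as healthy, so the upper end is cautious. A bias of 3-5 mm would need ill women to be left in altogether, which the article does not say will happen.

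**What to change.** Define exclusion from the centile data by serious illness diagnosed during pregnancy, with one common definition at all centres and regardless of birth weight. Do not use birth weight to decide who contributes. Make Eligibility criteria and Sample size state this same rule, including whether scans taken before the diagnosis are kept. Because all women are followed to the end, report the centiles with and without these women.

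The cost is wording and one agreed definition. Illness history, blood pressure and proteinuria are already recorded at each visit. A few more ill women with normal-weight babies leave the centile data: with 5% ill and a 0.5 SD effect, 7.0 − 1.5 = 5.5 more of 140 at a matching centre. Even with 15% ill, all ill women number 140 × 0.15 = 21, inside the allowance of 140 − 100 = 40, though that allowance must also cover loss to follow-up.
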